### Data collection

During both the baseline and intervention periods, patient data will be collected at four points in time: at enrollment, just prior to discharge, and at three- and six-month follow-up. Nursing staff will be surveyed just before and after implementation of the study intervention. To understand differences in performance of recommended actions across sites, we will track the fidelity with which clinician-focused elements of the intervention are implemented (*e.g*., attendance of staff nurses at training and feedback sessions, activity of peer leaders on each ward). Similarly, to understand differences in quit rates across sites, we will collect data regarding those elements of the intervention that are implemented for each study patient (*e.g*., delivery of bedside counseling, number of doses of pharmacotherapy provided, and number of telephone counseling sessions provided to patients referred to the quit line). With regard to the latter, we will also estimate the quit line connection rate by cross-referencing CPRS referrals of study patients for telephone counseling with actual quit line data [70].

### Patient-level data

After obtaining informed consent, the RA will perform a structured interview in current smokers to obtain more detailed information on smoking history (pack-years, number of quit attempts more than one day), other tobacco use (*e.g*., spit tobacco), alcohol use, overall health status, smoking-related medical comorbidities, readiness to quit smoking [23], level of tobacco addiction [71], perceived likelihood of staying off cigarettes after hospital discharge [72], and social support for quitting [6].

Just prior to discharge, the RA will ask eligible smokers whether they abstained from cigarettes during hospitalization, and whether or not the hospital staff had performed recommended smoking cessation counseling during the hospital stay. Patients will also be asked to specify whether they had received these services from their nurse, physician, or other clinician (*e.g*., respiratory therapist) [73]. Patient recall of advice to quit smoking has been shown to be reasonably accurate in assessing performance of guideline-recommended actions in clinical practice (sensitivity 92%, specificity 82% for advice to quit) [74].

At three- and six-month follow-up, research interviewers will contact patients by telephone about their smoking over seven days and 30 days prior to the interview (seven-day and 30-day, PPA), any quit attempts (>24 hours) since hospital discharge, and stage of change. At each follow-up, we will also determine prolonged abstinence (after a one-month grace period). All follow-up interviewers will be blinded to treatment assignment. Patients who report abstinence at six-month follow-up will be mailed a collection kit for salivary cotinine determination (with a follow-up telephone reminder to return the sample). A cutoff of 20 ng/ml will be used to determine abstinence, as this threshold is associated with high sensitivity and specificity (>90%) [75]. To calculate the biochemically confirmed six-month quit rate, we will adjust the seven-day PPA for the results of the cotinine analysis.

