### Study aims

The proposed study will test an implementation intervention to increase quit rates in hospitalized smokers in noncritical care settings by facilitating staff nurses' delivery of recommended smoking cessation services and reducing patient barriers to participation in cessation counseling. Of all the members of the inpatient team, VA staff nurses (including registered nurses (RNs) and licensed practical nurses (LPNs)) are best positioned to deliver a brief smoking cessation intervention because of their ready access to patients and education in patient education and counseling. Several controlled trials have demonstrated that nurse-delivered counseling can increase quit rates in hospitalized patients [19-22]. Although most of these trials have employed high-intensity interventions [11], low intensity counseling by staff nurses can also yield favorable results [23].

Thus, the primary aim of this practical clinical trial is to:

1. Determine the effect of a nurse-initiated intervention, which couples low intensity inpatient counseling with sustained proactive telephone counseling, on smoking abstinence in hospitalized patients.

Hypothesis 1a: Smoking cessation rates at three and six month follow-up, as measured by seven-day point prevalence abstinence (PPA) will be greater for intervention patients than usual care patients.

Hypothesis 1b: Intervention patients will be more likely to receive prescriptions for recommended pharmacotherapy for smoking cessation and referral to telephone counseling, compared to usual care patients.

To gain insight into mechanisms promoting the adoption of recommended practices by nurses and to determine the relative economic value of the intervention, key secondary aims are to:

1. Determine the impact of the intervention on nurses' attitudes toward and self-efficacy for providing smoking cessation counseling.

Hypothesis 2: Nurses attitudes toward cessation counseling and self-efficacy in providing such counseling will increase after being exposed to the intervention.

2. Identify barriers and facilitators to implementation of smoking cessation guidelines in VA hospitals and learn how to tailor the intervention to specific sites.

3. Determine the short-term cost-effectiveness of this implementation intervention.

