Patients who express an interest in quitting will be shown a 12-minute educational program on closed-circuit television, produced specifically for hospitalized VA smokers, and will receive a self-help guide to smoking cessation ('Clearing the Air: Quit Smoking Today', developed by the National Cancer Institute) [51]. Similar educational aids have been effectively used as an adjunct in counseling hospitalized smokers [7,20], and can reduce the time required for bedside counseling.

Nurses will be trained to electronically refer those patients who are willing and ready to make a quit attempt for proactive telephone counseling using a computerized referral process, based on evidence that VA patients who receive such counseling are more likely to quit [47]. Within 48 to 72 hours of discharge, a quit line counselor will call to confirm the patient's interest in quitting, congratulate the patient on his/her decision to stop smoking, and provide encouragement to reinforce self-efficacy. For those patients who are ambivalent about quitting, the counselor will focus on increasing motivation to quit. For those patients who remain committed to quitting, the counselor will focus on relapse prevention [52].

Follow-up calls will be made using a relapse-sensitive schedule (rather than at equal intervals) [13], with flexibility to accommodate the patient's needs (up to seven calls over three months) [47,53]. Telephone counselors will document the initial and follow-up contacts in CPRS using progress note templates for smoking cessation [54]. A final report summarizing events pertinent to the quit attempt will also be entered into CPRS shortly after the final counseling session (and will be mailed to the patient's non-VA primary care clinician, if applicable). Enabling bi-directional communication with primary care will integrate the telephone counseling into the patient's ongoing care [55,56]. We will also offer one additional course of quit line counseling for relapsed smokers (*i.e*., those who fail in their initial quit attempt).

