### Clinical information system

Presenting clinical reminders in a clear, simple format and coupling them with immediately actionable items is essential to enhance their effectiveness [57,58]. Streamlining the presentation of reminders and integrating them into the clinician's work flow is particularly important for nurses, who typically move rapidly from patient to patient, have little time to work through complex algorithms, and need information to be readily available [59]. The study team will work with nurse managers and CPRS clinical application specialists at each site to adapt the nursing intake form to reflect the five A's with the end-user in mind [60].

The smoking cessation template in CPRS will be designed to allow staff nurses to select and print patient self-help materials and to generate a consult for telephone care counseling. 'Quick orders' for pharmacotherapy will include recommended dosages for NRT, bupropion, and second-line therapies (and a list of contraindications to their use). The telephone care referral form will be adapted from 'fax to quit' forms that have been used successfully in primary care. System changes of this type can increase clinicians' ability to help patients quit smoking and their motivation to provide cessation counseling [18]. The research team at each site will query CPRS every two months to determine the proportion of smokers given assistance in quitting (referral for telephone counseling ordered, pharmacotherapy ordered), and these process measures will be presented to staff nurses during the intervention period.

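### One 20 ng/ml cotinine cutoff for all self-reported quitters counts abstinent nicotine-product users as smokers, so the confirmed (not the primary) six-month quit rate leans against the intervention

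*Protocol article*

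**What the plan says.** Patient-level data states who is tested: "Patients who report abstinence at six-month follow-up will be mailed a collection kit for salivary cotinine determination". It sets a single threshold, "A cutoff of 20 ng/ml will be used to determine abstinence, as this threshold is associated with high sensitivity and specificity" (given as above 90%), and then the use of the result: "To calculate the biochemically confirmed six-month quit rate, we will adjust the seven-day PPA for the results of the cotinine analysis". The article states no separate treatment of patients who take nicotine in another form, and names no other marker. Other tobacco use, with spit tobacco as the example, is recorded at enrollment but is not linked to the cutoff.

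The intervention works partly through drug treatment. Clinical information system describes quick orders that include "recommended dosages for NRT, bupropion, and second-line therapies". Hypothesis 1b in Study aims expects a difference between periods: "Intervention patients will be more likely to receive prescriptions for recommended pharmacotherapy for smoking cessation and referral to telephone counseling, compared to usual care patients". Sample size calculations puts receipt of recommended pharmacotherapy at 13% in the baseline period and powers the study for a seven-point difference, that is 20%.

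Statistical analysis defines the primary clinical endpoint as seven-day point prevalence abstinence (PPA) at three and six months, with no cotinine condition. Cost effectiveness analysis uses the self-reported quitter.

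**The concern.** Cotinine is a metabolite of nicotine and does not show where the nicotine came from. A patient who has stopped smoking but wears a patch or uses smokeless tobacco can exceed 20 ng/ml. The accuracy claimed for the cutoff cannot be assumed for such patients, and under the stated rule they become smokers.

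If this happened equally in both periods, it would shrink a true difference but create none. Here the protocol itself expects more pharmacotherapy in the intervention period. The better the process aim succeeds, the more true quitters the confirmed rate could lose in that period.

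This is an unrandomised before-after study with a self-reported primary endpoint, so the cotinine result is its only objective check on abstinence. A check that leans against the intervention could cast doubt on a real self-reported benefit.

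**Working it through.** **Inputs.** From Sample size calculations: six-month quit rate 12% at baseline, seven-point difference (19%), 500 patients per period, intracluster correlation (ICC) 0.01 for abstinence, pharmacotherapy 13% against 20%. From Statistical analysis: two-sided 0.05. From Table 1: 42 + 72 + 60 + 52 = 226 nursing staff. Not in the document, and varied below: the fraction f of pharmacotherapy recipients still using it at six months.

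**The plan's own figure.** Power for 12% against 19%, using the pooled two-proportion formula with n = 500/DE and DE = 1 + (m − 1) × 0.01, where m is the number of patients per nurse:
- no clustering: 86.5%
- m = 1,000/226 = 4.42, DE = 1.034, n = 483: 85.4%
- m = 10: 83.5%
- m = 15: 81.8%

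The article does not state m. The stated 83% is reached to within about a point with m of roughly 9 to 15, or with a continuity correction at m = 4.42 (about 83.2%). The sample-size figure is not in question.

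**Effect of the rule.** Assume that all pharmacotherapy is NRT, that quitters receive it at the 13% and 20% design rates, and that every current user exceeds 20 ng/ml. Then:
- confirmed rate, baseline = 0.12 × (1 − 0.13f)
- confirmed rate, intervention = 0.19 × (1 − 0.20f)

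The power column applies the design to the confirmed rate at DE = 1.034, for illustration only. The last column sets the true rate to 12% in both periods, which gives −0.12 × (0.20 − 0.13) × f.

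| f | Baseline | Intervention | Difference (points) | Power | Difference if no true effect (points) |
|---|---|---|---|---|---|
| 0 | 12.0% | 19.0% | 7.0 | 85.4% | 0 |
| 0.10 | 11.8% | 18.6% | 6.8 | 83.6% | −0.1 |
| 0.25 | 11.6% | 18.1% | 6.4 | 80.5% | −0.2 |
| 0.50 | 11.2% | 17.1% | 5.9 | 74.7% | −0.4 |
| 1.00 | 10.4% | 15.2% | 4.8 | 60.0% | −0.8 |

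**If use is concentrated among quitters.** Put the misclassified shares of true quitters in directly, again as assumptions:
- 10% intervention, 2% baseline: 0.19 × 0.90 − 0.12 × 0.98 = 5.3 points, power about 66%
- 20% intervention, 5% baseline: 0.19 × 0.80 − 0.12 × 0.95 = 3.8 points, power about 41%

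**If use is equal in both periods.** The difference is 0.07 × (1 − share): 6.65 points at 5% and 6.3 points at 10%. This is the relevant case for smokeless tobacco, since nothing in the intervention would raise its use.

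**The case against.** The strongest reply is that the confirmed rate is supplementary. It appears in one sentence and carries no hypothesis, test or power. This stands. A reader might infer that the trial's main result is biased; the documents do not support that, because the primary endpoint, the power calculation and the cost per quitter all rest on self-report.

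Second, the size is uncertain. The 13% and 20% cover all products, including bupropion, which does not raise cotinine, and they describe receipt rather than use at six months. If few patients still use NRT by then, the bias is small. A reader might assume much larger shares, such as 25% of intervention quitters against 10% at baseline, which gives 0.19 × 0.75 − 0.12 × 0.90 = 3.45 points. That has more quitters on nicotine at six months than the 20% design rate of ever receiving any pharmacotherapy, so it needs strong concentration among quitters, for which the document gives no evidence.

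Third, persistence to six months is inferred. Self-management support says "We will also offer one additional course of quit line counseling for relapsed smokers", after a first course of up to three months. A later quit attempt near the sampling point is therefore possible, but the sentence concerns counseling and does not mention NRT. Baseline patients also have access to drugs: Table 1 shows three of four sites providing pharmacotherapy without enrollment in a program.

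Fourth, the article says only that "we will adjust the seven-day PPA for the results of the cotinine analysis", and a fuller protocol or analysis plan may deal with nicotine users. This is fair, and no weight is placed here on an interview item that a condensed article may have left out. The point rests on the cutoff that the article does state. Doses provided (Data collection) and quantities dispensed (Cost effectiveness analysis) could flag likely users, but they record supply, not use in the days before the sample.

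**Conclusion.** The point holds, for the biochemically confirmed six-month rate only. As written, the rule counts abstinent nicotine-product users as smokers. To the extent that NRT use persists at six months and is higher in the intervention period, it biases that rate against the intervention.

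On the protocol's own pharmacotherapy figures the loss is modest: 0.2 to 1.1 points off a 7.0-point difference if 10% to 50% of recipients still use the product, and 2.2 points if all do. These figures assume that all pharmacotherapy is NRT and that all users exceed the cutoff, both of which push the loss up. They also assume that quitters use it no more than other patients; if they use it more, the loss is larger. It should be corrected because the remedy is cheap and because use at the time of sampling cannot be recovered later if it is not recorded.

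**What to change.** 1. At the six-month call, and again with the saliva kit, ask about any nicotine product or smokeless tobacco in the past seven days, worded identically in both periods.
2. Apply the 20 ng/ml rule only to self-reported abstainers who use no such product.
3. Report the confirmed rate twice: with users classified by self-report, and with all users counted as smokers.
4. Give the number of users by period.

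The cost is one question at two contacts and a few sentences of analysis text. The downside is that users go unverified, possibly more of them in the intervention period, so the self-report version may favour the intervention. Neither version should therefore be shown alone. The two versions bound each period's rate with respect to users; they bound the difference only if over-reporting among users is similar in the two periods, and this should be said when they are reported.

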### Nurse-level data

Pre- and post-intervention attitudes toward smoking cessation counseling will be measured by a decisional balance questionnaire that includes 10 items that reflect positive attitudes and 10 items that reflect negative attitudes toward the delivery of smoking cessation assistance [76]; in addition, we will also ask staff nurses about self-efficacy and role satisfaction in helping patients stop smoking [77]. As nursing performance can also be influenced by job satisfaction and work environment [78], the survey will also assess perceptions of professional status (using a seven-item subscale of the Index of Work Satisfaction [79]) and staffing and resource adequacy (using a four-item subscale of the Practice Environment Scale [80].

### Summative evaluation of the intervention

At the end of the intervention period, we will conduct semi-structured telephone interviews with approximately 32 patients. Within each site, we will randomly sample two intervention patients from each of four stage of change groups. Sampling for interviews will continue until data are saturated (*i.e*., when no new data are forthcoming in interviews within each site) [81]. The interviewer will initially ask the patient to describe his/her experiences with smoking and any conversations about smoking with hospital staff during the index hospitalization. Patients will then be asked to identify aspects of their interactions with the inpatient team that were most helpful and most difficult with regard to smoking cessation. Patients will also be asked about the transition to outpatient care and any attempts to maintain abstinence following hospital discharge. New questions will be added, and the original questions will be refined to capture issues emerging from the data as the interviews progress.

In order to evaluate the acceptability of the intervention to nursing staff and its likelihood of being maintained, we will conduct semi-structured, one-on-one interviews of one peer leader and a random sample of five staff nurses from each site (or until saturation is reached). The questions are designed to elicit stories from the staff nurses in an effort to capture how the intervention was implemented in practice [82]. In addition, they will be asked about the usefulness of the intervention, their future plans for using the intervention (or parts of it), and their suggestions for further refinements. All telephone interviews will be tape recorded, transcribed, and reviewed by the interviewer for accuracy.

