**Outcomes:**

The primary endpoint is seven-day point prevalence abstinence at six months following hospital admission and prolonged abstinence after a one-month grace period. To compare abstinence rates during the intervention and baseline periods, we will use random effects logistic regression models, which take the clustered nature of the data within nurses and hospitals into account. We will assess attitudes of staff nurses toward cessation counseling by questionnaire and will identify barriers and facilitators to implementation by using clinician focus groups. To determine the short-term incremental cost per quitter from the perspective of the VA health care system, we will calculate cessation-related costs incurred during the initial hospitalization and six-month follow-up period.

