## Methods

### Study design

This study is a before-after trial (with each site serving as its own control) in smokers who are hospitalized on the medical wards of four VA hospitals (Figure 1). After a six-month baseline period of enrollment, the research team will conduct focus groups of clinical staff at each site, adapt the strategy for guideline implementation, and train clinical staff at each site. A new cohort of study patients will be enrolled over the subsequent six-month intervention period. Staggering the timing of intervention across sites will allow us to collect concurrent control data for three of the four study sites during intervention; this will enable detection of system-wide trends in the delivery of cessation counseling, measurement reactivity, and other potential confounding factors within each period (except the final period)[24,25]. We considered cluster randomization by hospital, but the cost of conducting such a trial was not feasible due to budgetary constraints (as at least four sites per comparison group are typically required) [26].

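### Patient interviews timed to the end of the intervention period add a study contact about quitting to the intervention cohort only, mostly before the six-month outcome; the effect is small and cheap to avoid

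*Protocol article*

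**What the plan says.** Under Summative evaluation of the intervention, the protocol article states: "At the end of the intervention period, we will conduct semi-structured telephone interviews with approximately 32 patients". The sample comes from one cohort: "Within each site, we will randomly sample two intervention patients from each of four stage of change groups". The number is not capped, since "Sampling for interviews will continue until data are saturated". On content: "Patients will also be asked about the transition to outpatient care and any attempts to maintain abstinence following hospital discharge". Patients also describe their experience of smoking, their conversations about it with hospital staff, and what helped or was hard.

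Under Study design, the intervention period is an enrolment window: "A new cohort of study patients will be enrolled over the subsequent six-month intervention period". The abstract places the outcome later: "The primary endpoint is seven-day point prevalence abstinence at six months following hospital admission". The Statistical analysis section names both three and six months for the primary clinical endpoint.

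Under Data collection, both cohorts have the same four patient contacts: enrolment, before discharge, three months and six months. No interview of baseline patients is described. The Statistical analysis section analyses patients by the period in which they enrolled and does not mention the interviewed patients.

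**The concern.** The two cohorts are meant to differ in the intervention and otherwise to be followed alike. The interview is a further telephone conversation about smoking and quitting. It is not part of the intervention under test, and only intervention patients receive it. If it takes place before the outcome call, any response to it is counted in that cohort's abstinence rate and cannot be separated from the intervention effect.

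Study design relies on concurrent controls from the staggered sites to reveal measurement reactivity, among other things. Those controls have no such interview, so they cannot reveal reactivity that comes from it. At stake is a small shift in the primary comparison, most plausibly in favour of the intervention, although the documents do not establish the direction.

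**Working it through.** **Inputs from the protocol article**
- Four sites, four stage-of-change groups, two patients per group (Study design; Summative evaluation).
- 500 patients per period, a 12% baseline quit rate, and a planned difference of 7 points, so 12% against 19% (Sample size calculations).
- A six-month enrolment window (Study design) and an outcome six months after admission (Abstract, Outcomes).

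**Input assumed.** The lift in abstinence per interviewed patient is not in the documents. The range taken is 0 to 10 points.

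**Step 1: the plan's own count.** 4 sites × 4 groups × 2 patients = 32, which agrees with the stated figure. Share of the intervention cohort: 32/500 = 6.4%.

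**Step 2: timing.** A patient enrolled t months into the window has 6 − t months of follow-up when it closes. Only a patient admitted on the first day has reached six months. With uniform accrual (assumed), half have not reached three months. If interviews ran L months after the window closed, the share still short of six months would be (6 − L)/6:

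| Delay L (months) | Share short of six months |
|---|---|
| 0 | essentially 100% |
| 1 | 83% |
| 2 | 67% |
| 3 | 50% |
| 6 | 0% |

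**Step 3: shift in the quit rate.** Shift = (interviewed/500) × assumed lift, taking all 32 interviews to precede the outcome.

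| Assumed lift (points) | Shift (points) |
|---|---|
| 0 | 0 |
| 5 | 0.064 × 5 = 0.32 |
| 7 | 0.064 × 7 = 0.45 |
| 10 | 0.064 × 10 = 0.64 |

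The shift is proportional to the number interviewed. If saturation doubled it to 64 (an assumption), the 10-point lift would give 0.128 × 10 = 1.28 points.

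**Step 4: scale.** The standard error of the difference, ignoring clustering, is √[(0.12 × 0.88 + 0.19 × 0.81)/500] = √(0.2595/500) = 0.0228, or about 2.3 points. Suppose one interview did as much as the 7 points planned for the whole intervention. The shift of 0.45 points would then be 0.45/2.28, about one-fifth of a standard error. With no true difference at 12%, and again ignoring clustering, the two-sided error rate would rise from 0.050 to about 0.053 for a 5-point lift and 0.061 for a 10-point lift.

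**The case against.** The strongest reply is that the article never orders the interviews against the outcome calls. The end of the intervention period could be meant loosely, or could mean the end of that phase across the staggered sites, in which case patients at earlier sites might be past six months. The sampling strata point the same way: under Patient-level data, stage of change is named at the three- and six-month calls, whereas enrolment records readiness to quit. Sampling may therefore follow at least the three-month call. This stands in part: the order is an inference. But Study design and the Discussion both use the term for a six-month period. Even on the study-wide reading, patients at the last site would be short of six months, and a three-month call still precedes the six-month outcome.

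A second reply is that scheduling some 32 qualitative calls is detail that an article leaves to the full protocol. That would answer a missing time, but here a time is stated, and it is the stated time that creates the asymmetry.

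Third, the interview is retrospective and no advice is described, and both cohorts are already questioned about smoking and quit attempts. The marginal reactivity may be close to nil, which is why the assumed range starts at zero.

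A reader might also infer three stronger points that the documents do not support:
- **Compromised blinding.** The article says "All follow-up interviewers will be blinded to treatment assignment". Nothing suggests that these interviewers conduct or see the qualitative interviews, and intervention patients could already mention their counselling.
- **A much larger bias.** A 20-point lift from one evaluative call would be nearly three times the 7 points planned for bedside counselling, pharmacotherapy and up to seven counselling calls together.
- **Interviews that fail their own purpose because they miss the full six months.** The topics are mainly the hospital stay and the transition after it, and no section requires a six-month account.

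**Conclusion.** The point holds as a minor one. On the natural reading, about 6.4% of the intervention cohort, more if saturation requires, would have an additional study contact about quitting, most of them before their six-month outcome, with no counterpart in the baseline cohort. The shift is 0 to about 0.6 points against a planned 7. That rests on 32 interviews, all before the outcome, and on a lift of 0 to 10 points per interviewee, which is assumed. The asymmetry could not by itself produce the planned effect and does not put the main conclusion in doubt. It is worth removing because it is avoidable and the concurrent controls cannot detect it.

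**What to change.** State in Summative evaluation of the intervention that a patient is interviewed only after that patient's own six-month outcome call, and cotinine kit if one was sent, is complete. The site and stage-of-change strata can stay, with the date of the stage assessment given. Sample size, power and staffing do not change. The cost is that interviews finish later and recall of a brief bedside conversation is older.

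If earlier interviews are preferred to protect that recall, which is a defensible choice, keep them and prespecify a sensitivity analysis of three- and six-month abstinence that excludes interviewed patients. The cost is one additional analysis.
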